## Methods/Design

### Patients

In 11 hospitals in the Netherlands, all patients with advanced colorectal, breast, or ovarian cancer who have started treatment with first-line palliative chemotherapy and upon disease progression will be faced by the choice regarding second-line palliative chemotherapy will be included. Exclusion criteria are labile personality structure, as assessed by the physicians, a Karnofsky performance score lower than 60, and insufficient knowledge of the Dutch language. The study has been approved by the research ethics committees of all participating hospitals.

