### Randomization

Randomization will be performed to determine whether the patient will receive usual care (n = 70) or usual care plus the decision aid (n = 100). To accomplish this, a computer generated randomization list is prepared that is stratified by hospital, using a block size of 3. Each participating hospital will receive three sets of sealed envelopes, related to colorectal, breast, and ovarian cancer patients. When disease progression is diagnosed by the oncologist, a nurse will perform the randomization by opening the appropriate envelope.

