### Sample size calculation

Our primary research question is whether or not patients want to be informed. For study question 1a, about 100 patients in the intervention group will suffice to estimate an assumed desire rate for prognostic information of 80% with 95% confidence interval from 71% to 87%. For study question 1b, regarding factors that determine information desire, again about 100 patients will suffice to detect a weak correlation of 0.28 between a predictor and information desire, with α = 0.05 and a power equal to 0.82. For question 2, dealing with the ability of the medical oncologist to judge whether or not the patient wants this information, the same analysis applies as for study question 1b. For study question 3, which addresses the effect of the introduction of decision support compared to usual care on patient well-being, the intervention group is compared to the usual care group. Because one of the main concerns of physicians is that information on prognosis provokes anxiety, anxiety is used as the main outcome measure. We assume that the HADS anxiety difference between the two groups at t3 is equal to 2.2, and the correlation between the measurements at t1 and t3 equals 0.72. The standard deviation in each cell is about 6, corresponding to a medium sized effect size of 0.36. With α = 0.05, and 70 patients in each group, the power to detect the assumed effect is equal to 0.81. In conclusion, 100 patients in the intervention group and 70 patients in the usual care group suffice to answer the above research questions. Assuming that 30% of the patients refuse to give informed consent, and that 1% of patients has died at t3, 246 patients will have to be approached.

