### Statistical Analysis

In all the analyses, scale values will be calculated only if at least half of the items are available, by imputing the mean of the available items. Question 1a about the information desire will be answered by calculating the desire rate for prognostic information with a 95% confidence interval. For question 1b, which factors determine information desire, patients will be grouped according to information desire, ranging from 0 (no information desired) to 3 (information on serious adverse events, tumour response, and survival desired). Then comparisons between these four groups will be made. For categorical variables, the Chi-square test will be used. Continuous data will also be analyzed using the Chi-Square test, after a median-split subdivision into two categories. The HADS scores will be divided by use of a clinical cut-off point of 8 [17,30,31]. Bivariate analyses will be presented with p-value of variables related with information desire at the level of p < 0.2. Finally, these variables will be entered simultaneously in a regression model.

For question 2, agreement between the substitute judgment of the oncologist and the patient information desire is determined. Agreement can arise from chance; a measure correcting for chance agreement is the κ statistic, ranging from 0 to 1. A κ of 0.2, 0.5, and 0.8 indicates poor, moderate, and good agreement, respectively [32,33]. In bivariate and multivariate analyses, associations will be sought between agreement and patient variables (sociodemographic, medical, psychological, knowledge and information). Dichotomized variables associated with agreement at a level of p < 0.2 will be entered simultaneously in a regression model.

Question 3, which addresses the effect of the introduction of decision support compared to usual care on patient well-being, will be answered by comparing the intervention group with the usual care group. Analyses of covariance corrected for differences at baseline are used to test the effect of the intervention. For group comparisons at a single point in time, a t test will be performed for continuous variables and the Chi-square test for categorical variables.

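### Randomization is stratified by hospital and tumour type, but no question 3 analysis names either factor and the t and Chi-square tests cannot include them: a small, conservative loss of precision

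*Protocol article*

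**What the plan says.** **Design.** Under Randomization, "a computer generated randomization list is prepared that is stratified by hospital, using a block size of 3". The same section adds: "Each participating hospital will receive three sets of sealed envelopes, related to colorectal, breast, and ovarian cancer patients". The Patients section gives the number of sites: "In 11 hospitals in the Netherlands". Read together, allocation is restricted within as many as 11 × 3 = 33 hospital-by-tumour cells.

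**Analysis.** Under Statistical Analysis, question 3 (decision aid against usual care) has two parts. The first is: "Analyses of covariance corrected for differences at baseline are used to test the effect of the intervention". The second is: "For group comparisons at a single point in time, a t test will be performed for continuous variables", with the Chi-square test for categorical variables. The section lists no ANCOVA covariates and mentions neither hospital nor tumour type for question 3.

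**Main outcome.** Under Sample size calculation, for question 3, "anxiety is used as the main outcome measure". The planning inputs are a "HADS anxiety difference between the two groups at t3 is equal to 2.2, and the correlation between the measurements at t1 and t3 equals 0.72", with a standard deviation of about 6, 70 patients per group and a stated power of 0.81.

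**The concern.** Stratified allocation balances the arms on the strata, so the treatment estimate varies less from one possible randomization to the next. An analysis that omits the strata still counts stratum-to-stratum variation as noise. Whenever the strata are related to the outcome, its standard error is therefore larger than the estimate's true variability.

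The mismatch is firmest for the single-time comparisons, because the methods named there have no place for a covariate. Table 1 shows several outcomes collected only after the decision, with no t1 value to adjust for: perceived involvement, undesired information, balanced presentation, objective knowledge, risk perception and the decision evaluation scales. Tumour type could plausibly matter for some of these. A separate aid is built for each tumour type from its own systematic review, and patients are asked to estimate the chance of severe diarrhoea and of a response.

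For anxiety, the trial asks whether prognostic information does harm. An inflated standard error makes a real increase easier to miss, and a null result easier to read as reassurance.

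**Working it through.** **1. Inputs from the protocol article.** Difference 2.2, SD 6, t1–t3 correlation r = 0.72, α = 0.05 (two-sided assumed), 70 per group for power, 170 in all, 11 hospitals, 3 tumour types, blocks of 3.

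**2. The plan's own figure.** The change-score SD is 6 × √(2 × (1 − 0.72)) = 4.49. With 70 per group, power is 0.826 (normal) or 0.821 (noncentral t), so the stated 0.81 reproduces to within 2 points. ANCOVA has residual SD 6 × √(1 − 0.72²) = 4.16. Its power is about 0.87 to 0.88 with 70 per group and about 0.92 with 100 and 70. None of these figures depends on the strata.

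**3. Effect of leaving the strata out (assumed inputs).** The documents give no between-hospital or between-tumour variance, so the strata's share of the residual variance is varied from 0% to 30%. Each setting is 3,000 simulated trials of 170 patients in 11 hospitals and 3 tumour types. Permuted blocks of 3 are used within each hospital-by-tumour cell, with 2:1 allocation assumed. ANCOVA on the t1 score alone is compared with ANCOVA on the t1 score plus hospital and tumour type as fixed main effects, at r = 0.72. Monte Carlo error is about 0.004 for type I error and 0.005 for power.

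| Stratum share | Type I error, without → with | Power, without → with |
|---|---|---|
| 0% | 0.053 → 0.054 | 0.897 → 0.888 |
| 5% | 0.044 → 0.050 | 0.903 → 0.904 |
| 10% | 0.043 → 0.049 | 0.908 → 0.917 |
| 20% | 0.043 → 0.055 | 0.922 → 0.944 |
| 30% | 0.027 → 0.046 | 0.942 → 0.971 |

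**4. Size of the standard-error excess without the strata.** Mean model SE divided by the true SD of the estimate:
- 10% share: 0.670 / 0.650 = 1.03
- 20% share: 0.661 / 0.630 = 1.05
- 30% share: 0.652 / 0.579 = 1.13

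The simple formula 1 − √(1 − 0.10) = 5.1% overstates the 10% case because it assumes full balance within strata. With 170 / 33 ≈ 5 patients per cell, many blocks of 3 stay incomplete.

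**5. Unadjusted t test on t3 anxiety, same trials.** The strata's share of total variance is the residual share times 1 − 0.72² = 0.48, so 10%, 20% and 30% become 4.8%, 9.6% and 14.4%. The SE ratios are 0.970 / 0.970 = 1.00, 0.963 / 0.943 = 1.02 and 0.956 / 0.893 = 1.07. Type I error is 0.052, 0.038 and 0.040. At a 0% share it came out at 0.059. The test is exact there, so that excess is simulation noise.

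**6. Weaker baseline correlation.** The Discussion warns that the t1-to-follow-up correlation may be weakened but gives no value. At an assumed r = 0.50 the residual SD is 6 × √(1 − 0.50²) = 5.20. In 4,000 trials per setting, type I error at a 10% share is 0.041 without and 0.052 with the factors. Power is 0.751 without and 0.776 with, a difference of 2.5 points. At a 0% share power is 0.738 without and 0.734 with.

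**The case against.** The best defence is that this is a condensed article. A covariate list is commonly left to the full protocol or analysis plan, and silence about it is not an error. That stands for the ANCOVA. A reader might infer that the ANCOVA ignores both factors, but the text lists no covariates and excludes none. It does not stand for the single-time comparisons, where the article fixes methods that cannot hold the factors.

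The defence is also right on direction and size. A reader might infer that the standard errors are wrong in a way that undermines the results. They would be too large, not too small, and the effect on power is about a point for modest stratum shares at the stated correlation. No passage says that hospital or tumour type predicts anxiety beyond baseline anxiety, or that usual-care information differs between hospitals. Question 3 is also not the primary question.

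Two further inferences are not supported:
- The correction for baseline differences could be read as letting observed imbalance choose the covariates. The sample-size section uses the t1–t3 correlation, and the Discussion describes a baseline measurement for the effect, so adjustment for the t1 score is the ordinary reading.
- The ANCOVA could be read as using t3 alone and losing patients who answered only at t2. The section does not say so, and this has nothing to do with stratification.

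**Conclusion.** The point holds as a modest mismatch between design and analysis. Allocation is stratified by hospital and, on the natural reading of the envelope sets, by tumour type. No question 3 analysis names either factor, and the t and Chi-square tests cannot include them.

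If the strata explain up to 10% of the residual variance, the ANCOVA standard error without them is up to about 3% too large and type I error is at or below 5%, within simulation error. The power lost is about 0 to 1 point at r = 0.72, or 2 to 3 points at a 10% share with r = 0.50. Shares of 20% to 30% would cost 2 to 3 points at r = 0.72. The shares and the value 0.50 are assumptions. The error is conservative, so a positive finding is not invalidated. It matters mainly because the main question 3 outcome is a possible harm, for which a missed effect is the costlier mistake.

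**What to change.** State that the question 3 ANCOVA includes the t1 score, tumour type and hospital, regardless of observed imbalance. Enter the two factors as main effects rather than as up to 33 cells, with hospital random or small hospitals pooled. For outcomes compared at a single time, replace the t and Chi-square tests with linear or logistic models, or stratified tests such as Cochran-Mantel-Haenszel, using the same factors.

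The change is to wording only, since both factors are known at randomization. If both are fixed, they use up to 10 + 2 = 12 degrees of freedom. If the strata have no effect, the adjusted ANCOVA loses about one power point (0.897 to 0.888 in the simulation at r = 0.72). With about 170 / 11 ≈ 15 patients per hospital, logistic models with hospital terms may be unstable for uncommon binary outcomes. Pooling or a stratified test is the safer choice there.

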#### Coping

Coping with cancer is assessed with the Mental Adjustment to Cancer scale [21]. Three coping strategies are assessed: helplessness/hopelessness, avoidance, and fighting spirit. The patient's decision style is assessed with The Michigan Assessment of Decision Style (MADS) [22]. The MADS covers (1) avoidance (four items, e.g. 'I prefer not knowing the possibility that unexpected things could happen to me'); (2) deferring responsibility (three items, e.g. 'I would follow the recommendations of my physician'); (3) information seeking (four items, e.g. 'I would spend as much time as I could gathering information'); and (4) deliberation (five items, e.g. 'I would carefully consider the risks of each option as I was making a choice'). The general participation preference at baseline is measured with the two decision-making items from the Problem-Solving Decision-Making Scale [23]. The questions are as follows: 'When the risks and benefits of the treatment options are known to you, (1) who decides how acceptable those risks and benefits are for you and (2) who decides what treatment should be selected?'. Answers range from 'only the physician' to 'only me'. Perceived participation is assessed by the same questions in past tense, after the decision is made. Perceived involvement is measured by asking patients whether they felt they were offered a choice between BSC plus chemotherapy and BSC alone [24]. In addition, patients are asked whether their opinion regarding the treatment mattered. Both questions use a yes/no response. Death avoidance will be measured by means of the Death Avoidance Scale, which was adapted by Kaplowitz *et al*. 2002 [25] from the original Death Acceptance Scale developed by Klug and Sinha (1987) [26]. The two items are as follows: 'I avoid discussing death when the occasion presents itself' and 'I make a conscious effort to avoid dwelling on thoughts of death', and are measured on a 5-point scale (1 = strongly disagree, 5 = strongly agree).

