#### Information

The preferred amount of information is measured on a 11-point scale ranging from 0 (I want to know nothing about the illness and its treatment) to 10 (I want to know everything there is to know about the illness and its treatment) [8]. The amount of information received about the treatment choice is measured on a 7-point scale ranging from 1 (I received way too little information), 4 (I received exactly enough information), to 7 (I received way too much information). Information received during the consultation with the oncologist, regarding adverse events, tumour response, and survival, is assessed using a yes/no response. Whether patients received any undesired information is asked with a question using a yes/no response. The key variable information desire is described under 'Interview' above. Satisfaction with the quality of information is asked with three questions related to information on adverse events, tumour response, and survival. Responses are on a 6-point scale ranging from 1 (not satisfied) to 6 (very much satisfied). The balanced presentation of information is evaluated on a 5-point scale from 1 (clearly in favour of chemotherapy plus BSC), 3 (balanced), to 5 (clearly in favour of BSC alone). Six questions are asked about unpleasant, shocking, frightening, and threatening experiences with the information received, measured on a 5-point scale from 1 (no negative experience) to 5 (very negative experience). Numeracy, i.e. the ability to handle basic probability concepts, needed for the interpretation of risk information, is measured by the Subjective Numeracy Scale (SNS) [27].

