#### Knowledge

Patients rate their own knowledge (subjective knowledge) on cancer treatments with a single question on a 10-point scale ranging from 1 (very bad) to 10 (excellent). Two questions are asked to assess the subjective knowledge with respect to risks and benefits of treatment options on a 10-point scale. Objective knowledge will be measured with a questionnaire containing five statements related to the two options BSC plus chemotherapy and BSC alone. These statements have to be judged as right or wrong. Subjective risk perception is measured by three questions on the chance of experiencing a serious adverse event from 1 (very high) to 5 (very low), the chance that stable disease or a response will be achieved by BSC plus chemotherapy, as opposed to BSC alone from 1 (much higher) to 7 (much lower), and the chance of experiencing pain on treatment with BSC plus chemotherapy, as opposed to BSC alone from 1 (much higher) to 7 (much lower). Objective risk perception is asked for the chance of experiencing severe diarrhoea, and the chance of achieving a response. Patients are asked to give a risk estimate for these two outcomes in a range from 0% to 100%.

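### Treatment subjective knowledge and, on the natural reading, perceived participation are compared by an unadjusted t test although related t1 measures are already collected; adjusting for them is a cheap improvement

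*Protocol article*

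**What the plan says.** The Statistical Analysis section of the protocol article gives two methods for question 3. The effect of the intervention is tested by analysis of covariance that adjusts for baseline. A second sentence then says: "For group comparisons at a single point in time, a t test will be performed for continuous variables and the Chi-square test for categorical variables". No covariate is named in that sentence, and the section does not list which outcome goes to which method.

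Table 1 and the measure descriptions show what is available for two of the outcomes:

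- **Knowledge.** At t1 patients rate their knowledge of cancer treatments with one question on a 10-point scale. At t2 only, according to the Knowledge section, "Two questions are asked to assess the subjective knowledge with respect to risks and benefits of treatment options on a 10-point scale".
- **Participation.** At t1 the two Problem-Solving Decision-Making items ask who should decide. At t2 and t3, according to the Coping section, "Perceived participation is assessed by the same questions in past tense, after the decision is made".

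Under Procedure and Randomization, the t1 questionnaire is sent during first-line treatment and randomization follows at progression. Both t1 measures therefore precede allocation. On the choice of main outcome for question 3, the Sample size calculation states that "anxiety is used as the main outcome measure".

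**The concern.** Research question 3 (end of the Background) covers information and decision related outcomes as well as well-being, and only anxiety has a power calculation. For an outcome compared by a plain t test, all variation between patients stays in the error term, including any part that a t1 measure could explain. A chance difference between groups in prior knowledge or in preferred role is also left unadjusted in the estimate.

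What is at stake is precision, not validity. An effect of the aid on knowledge or participation would be estimated with a somewhat wider interval than necessary, from data that every participant is asked to supply anyway.

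**Working it through.** **1. The plan's own figure.** Inputs from the Sample size calculation: "We assume that the HADS anxiety difference between the two groups at t3 is equal to 2.2"; "The standard deviation in each cell is about 6, corresponding to a medium sized effect size of 0.36"; a t1–t3 correlation of 0.72; and "With α = 0.05, and 70 patients in each group, the power to detect the assumed effect is equal to 0.81". Sidedness is not stated, and a two-sided test is assumed here.

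- SD of the change score = 6 × √(2 × (1 − 0.72)) = 4.49.
- With a difference of 2.2 and 70 per group, power is 0.826 (normal) or 0.821 (noncentral t).
- With the rounded effect size, the difference is 0.36 × 6 = 2.16, and power is 0.812 or 0.807.

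The stated 0.81 is reproduced. It relies on the baseline measurement: without it (SD 6, difference 2.2, 70 per group) power is 0.583. Under the analysis of covariance in the plan, the SD is 6 × √(1 − 0.72²) = 4.16, and power is 0.878 with 70 per group and 0.924 with 100 v 70. The main outcome therefore already benefits from adjustment.

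**2. Which outcomes the t test sentence covers.**

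| Outcome | Measured | Own t1 value | Related t1 measure | Falls under the t test? |
|---|---|---|---|---|
| HADS anxiety | t1, t2, t3 | yes | – | no |
| Treatment subjective knowledge | t2 | no | general subjective knowledge, 10-point | yes, plainly |
| Perceived participation | t2, t3 | no | participation preference, same two items | natural reading, not stated |

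**3. What adjustment could gain.** The article gives neither an effect size nor a correlation for these two outcomes, so both are assumptions. The standardized effect of 0.36 is borrowed from anxiety, and the correlation ρ is varied. With n₁ = 100, n₂ = 70 and two-sided α = 0.05:

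- noncentrality = d / √(1 − ρ²) × √(n₁n₂ / (n₁ + n₂))
- √(7000 / 170) = 6.417, so at ρ = 0 the noncentrality is 0.36 × 6.417 = 2.31
- df = 168 for the t test and 167 with one covariate

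| ρ | residual variance 1 − ρ² | power |
|---|---|---|
| 0 (t test) | 1.00 | 0.632 |
| 0.2 | 0.96 | 0.650 |
| 0.3 | 0.91 | 0.673 |
| 0.4 | 0.84 | 0.707 |
| 0.5 | 0.75 | 0.756 |

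**4. A check that does not borrow the anxiety effect.** Take instead whatever effect the t test would detect with 80% power at 100 v 70 (normal approximation). Adjustment then gives 0.816 at ρ = 0.2, 0.836 at 0.3, 0.864 at 0.4 and 0.899 at 0.5. The equivalent gain in sample size, 1 / (1 − ρ²) − 1, is 4%, 10%, 19% and 33%. The pattern is the same: under 2 points at ρ = 0.2 and about 10 to 12 points at ρ = 0.5.

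**The case against.** The strongest reply is that nothing here is wrong. Under randomization the unadjusted t test is unbiased, and its error rate already allows for chance imbalance. Using analysis of covariance where an outcome has its own baseline, and a t test where it has none, is a coherent rule. The outcomes are secondary, and the choice of proxy covariates is often left to an analysis plan. All of this stands, which is why the point is an improvement and not an error. It remains worth making because the article does name a method for these comparisons, and that method has no covariate.

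Four stronger readings are tempting, and the article does not support them.

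- **That t1 holds a near-identical baseline.** Preferring to decide is not the same as having decided. General knowledge of cancer treatments during first-line therapy is not knowledge of the risks and benefits of the second-line options. The measures are related, not repeated. Adjustment needs only a prognostic covariate, so the proposal survives, but a high correlation cannot be presumed.
- **That perceived participation is expressly assigned to the t test.** This is an inference: it is measured twice, and the analysis of covariance sentence is not restricted to outcomes with an identical t1 item. Treatment subjective knowledge does not depend on this inference.
- **That numeracy should be the covariate for the risk estimates.** The Information section says: "Numeracy, i.e. the ability to handle basic probability concepts, needed for the interpretation of risk information, is measured by the Subjective Numeracy Scale". That bears on the accuracy of an estimate. The outcome is a raw percentage from 0 to 100, and nothing in the article implies a linear relation between the two.
- **That power is demonstrably lost.** No correlation is given for either pair. The Discussion warns that the interval between t1 and follow-up may weaken correlations even for the effect measures themselves.

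**Conclusion.** The point holds as a cheap improvement. For treatment subjective knowledge the stated method is an unadjusted t test although a related pre-randomization self-rating on a 10-point scale is collected. For perceived participation the same is true on the natural reading.

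The gain cannot be fixed from the article. It rests on an assumed correlation and on a borrowed effect size of 0.36. Under those assumptions it runs from about 2 percentage points of power at a correlation of 0.2 to about 12 at 0.5, and given the Discussion's own warning it may well lie near the lower end. A reader might infer that the question 3 conclusion is at risk. It is not: anxiety is already baseline-adjusted, and the t test comparisons remain valid.

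**What to change.** In the Statistical Analysis section, qualify the t test sentence for continuous outcomes along these lines: *continuous question 3 outcomes without a t1 value of their own are compared by analysis of covariance on a prespecified related t1 measure where one is named, and by t test otherwise*. Name the two pairs:

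- treatment subjective knowledge (t2), adjusted for general subjective knowledge (t1);
- perceived participation (t2 and t3), adjusted for participation preference (t1).

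Naming the covariates before the data are analysed also removes any post hoc choice, and it settles which method applies to perceived participation.

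The cost is one sentence, one degree of freedom per model, and a simple rule for patients with a missing t1 item. No new data, visits or patients are needed.
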